## 1 Trial Identification

The EudraCT number for this protocol is 2019-004209-28. The protocol code number is SP001-001.

## 2 Introduction and Rationale

### 2.1 Background

Urinary tract infections (UTI) are one of the most common infectious diseases in the world, affecting approximately 150 million people each year. The most common form of UTI is bacterial cystitis, which mainly affects women and is frequently recurring. A history of acute cystitis constitutes the greatest risk factor for recurrent cystitis. The global epidemic of antibiotic resistant bacteria is alarming, making these infections increasingly difficult to treat and the need for treatment alternatives quite urgent. WHO describes antibiotic resistance as one of the biggest threats to human health globally.

In recent years, new knowledge has defined molecular mechanisms and partly explained the link between infection, inflammation and pain in the bladder. Our research has shown that acute cystitis is caused by hyper-inflammation of the bladder and surrounding structures caused by Interleukin-1, which drives the disease process. As a result, blockade of the IL-1 receptor (IL-1R) with an IL-1R antagonist (Anakinra) protects against acute cystitis in animal models. In animal models, we have also defined how IL-1 overactivation occurs molecularly and how IL-1 drives the inflammatory process in the lower urinary tract [1]. It has also been shown in a clinical study that patients with acute cystitis have elevated levels of IL-1 in urine [1]. These findings illustrate for the first time the immunological background to acute cystitis and demonstrate Kineret's potential for the treatment of acute cystitis in humans.

Kineret® (Anakinra) is a recombinant IL-1R antagonist that has been approved for clinical use to treat various rheumatological diseases [2]. Treatment is chronic in many cases and well tolerated with an extensively documented safety profile. In exceptional cases, treatment may increase the risk of infections, primarily within the respiratory tract [3-5]. We have not found any support in the literature that prolonged Kineret® treatment would cause any risk of UTI.

This is in good agreement with our research results identifying specific immunological mechanisms linked to UTI and specifically acute cystitis. In an animal model, Kineret® was shown to inhibit the inflammatory process of the bladder during acute cystitis [1]. The inhibited inflammatory response in turn lead to decreased bacterial levels, an effect comparable to antibiotic therapy, and partly to rapidly decreasing symptoms.

Clinical Trial Protocol

Interest in the use of anti-inflammatory drugs has increased in recent years, mainly in the form of NSAIDs, as an alternative to antibiotic therapy for uncomplicated cystitis with varying results [6]. The studies show that NSAIDs can be useful for treatments of acute symptoms and may slightly decrease recurrent cystitis, but due to a lack of specificity, these anti-inflammatory agents cannot completely replace antibiotics in the treatment of acute cystitis [7-9]. We believe that our strategy, to block the IL-1 receptor, has a much more precise and well-defined molecular mechanism as well as extensive support in experimental models.

Based on the research results described above, we want to evaluate the possibility of treating recurrent acute cystitis with Kineret. We want to investigate whether the treatment provides adequate cure for acute cystitis compared to conventional antibiotic treatment, both based on the patient's symptoms and inflammation and on the effects on bacteria in the urine.

## **2.2 Clinical experience with Kineret**

### **Rheumatoid Arthritis (RA)**

Kineret has been used for years in combination with methotrexate for the treatment of symptoms in adults with RA who do not respond adequately to methotrexate alone. The recommended dose of Kineret is 100 mg administered subcutaneously once daily. The dose should be given at approximately the same time each day. Kineret is ready for use in a graduated pre-filled syringe. The graduated pre-filled syringe allows doses between 20 and 100 mg.

### **Pharmacokinetics**

The absolute bioavailability of Kineret following a 70 mg subcutaneous bolus injection in healthy subjects (n = 11) is 95%. After a subcutaneous injection, the absorption process is the rate limiting factor for the elimination of plasma Kineret. In rheumatoid arthritis subjects, maximal plasma concentrations of Kineret were reached 3 to 7 hours after subcutaneous administration of Kineret at clinically relevant doses (1 to 2 mg/kg; n = 18). Plasma concentration decreased without any noticeable distribution phase and the elimination half-life was between 4 and 6 hours. In patients with rheumatoid arthritis, no unexpected accumulation of Kineret was observed after daily subcutaneous doses for up to 24 weeks. Mean (SD) estimates of clearance (CL / F) and volume of distribution (Vd / F) by population analysis of data from two PK studies in 35 patients with rheumatoid arthritis were 105 (27) ml / min and 18.5 (11) liters, respectively [10, 11]. Data from humans and animal data showed that the

elimination of Kineret is mainly via the kidneys. Clearance of Kineret in patients with rheumatoid arthritis increased with increased creatinine clearance.

The effect of demographic differences on the pharmacokinetics of Kineret was studied by pharmacokinetic analysis of the population of 341 patients who received daily subcutaneous injections of Kineret at doses of 30, 75 and 150 mg for up to 24 weeks [10, 12]. The estimated clearance of Kineret increased with increased creatinine clearance and body weight. The pharmacokinetic analysis of the population showed that the mean plasma clearance after subcutaneous bolus administration was approximately 14% higher for men than for women and approximately 10% higher for subjects <65 years compared to subjects  $\geq$  65 years. After adjusting for creatinine clearance and body weight, gender and age were not significant factors for the mean plasma clearance. No dose adjustment is required based on age or gender.

## 2.3 Pre-clinical findings

An *in vivo* study published in 2016 identified acute cystitis as an Interleukin-1beta (IL-1 $\beta$ )-driven, hyper-inflammatory condition of the infected urinary bladder and IL-1 receptor blockade as a novel therapeutic strategy. In the study, the disease severity was controlled by the mechanism of IL-1 $\beta$  processing and mice with intact inflammasome function developed a moderate, self-limiting form of cystitis [1]. A second study showed that infection activates Neurokinin-1 receptor (NK1R) and Substance P (SP) expression in nerve cells and bladder epithelial cells *in vitro* and *in vivo* in the urinary bladder mucosa by an IL-1 $\beta$  driven mechanism [13]. The suggested clinical relevance was supported by elevated urine SP levels in patients with acute cystitis, compared to patients with asymptomatic bacteriuria. Blocking of IL-1 $\beta$  receptor was proposed to control pain and mucosal inflammation [13].

## 2.4 Trial Rationale

### 2.4.1 Overall Trial Rationale

The overall rationale of this pilot trial is to investigate whether Kineret may offer patients with recurrent acute cystitis an alternative treatment to that of antibiotics. Due to the increased development of resistance to antibiotics, there is a need of alternative treatments.

Acute cystitis is common and the disease burden is especially great in patients with recurrent infections, which can result in a markedly reduced quality of life and debilitating pain syndromes. This study is based on novel findings that define the mechanism of acute cystitis, including the inflammatory signalling cascades that are activated by the bacteria and the host

immune defects that allow infection to occur and recur in specific individuals. Effective treatment was achieved in an animal model, using Kineret [1, 13]. This included mice with genetic immuno-deficiencies that would have suffered from very severe disease if not treated. Importantly, this treatment both reduced inflammation in the tissue and improved bacterial clearance, a combination which would be extremely important to achieve in the clinic, not least in patients with infections caused by antibiotic resistant strains.

#### **2.4.2 Rationale for safety**

The clinical safety and tolerability of Kineret administration has been well documented as Kineret is a registered drug. In 2002 Kineret received a marketing authorisation valid throughout the European Union. Kineret is used to treat various rheumatological diseases and treatment is in many cases chronic. The safety profile of Kineret has thus been studied extensively in clinical use as well as in a large number of placebo controlled studies. The side effects of Kineret have been documented to be mostly mild [10].

#### **2.4.3 Rationale for efficacy**

Kineret is a recombinant human IL-1 receptor blocker. This molecule has been used for many years in the treatment of arthritis, but also in other diseases where acute inflammation causes harm to the patient. We could see that Kineret has shown similar efficacy as antibiotics in an animal cystitis model that mimics human disease quite closely [13]. From our studies in mice, we observed that inhibition of uncontrolled inflammation cures urinary tract infection faster and without organ damage [1, 13]. In this trial we will follow well established guidelines for antibiotic therapy, such as the German AWMF S3 guideline management of uncomplicated UTI (AWMF 043/044)

([https://www.awmf.org/uploads/tx\\_szleitlinien/043-044k\\_S3\\_Harnwegsinfektionen\\_2017-05.pdf](https://www.awmf.org/uploads/tx_szleitlinien/043-044k_S3_Harnwegsinfektionen_2017-05.pdf)).

Recurrent acute cystitis occurs in a subset of patients with elevated susceptibility, possibly due to a less effective immune system. Kineret will be used as a way of compensating this defect in the patients and improve the clearance of infection.

#### **2.4.4 Rationale for female patients**

The disease uncomplicated (recurrent) cystitis occurs only in women. Therefore, only female patients are included in this clinical trial.

### **2.4.5 Rationale for lifestyle considerations**

Since CYP450 food products like grapefruit and herbal products like St. John`s wort may interact with the study medication, patients are instructed to waive such products while participating in this clinical trial.

## **2.5 Ethical and Legal Consideration Statement**

The information in this clinical trial protocol (CTP) is consistent with current knowledge of the risks and benefits of the study drugs as well as the ethical and scientific principles set out in the Declaration of Helsinki and the guidelines for Good Clinical Practice (GCP). The protocol is thus designed to ensure that the Sponsor, its designee and site staff conduct the trial according to the ethical and scientific principles governing clinical research.

The investigator must ensure that patients` anonymity will be maintained and that their identities are protected from unauthorized parties in accordance with General Data Protection Regulation (GDPR) requirements.

Competent Authority (CA) approval as well as approval of the Independent Ethics Committee (IEC) must be in place prior to trial start.

Essential amendment to the trial protocol will not be implemented by either the Sponsor or the Investigator without agreement by both parties and prior to written approval by CA and IEC as required. Exceptions to this is a change of set protocol procedures to eliminate immediate hazards to participating patients. A protocol amendment will then retrospectively be submitted to the CA/IEC for approval. Any deviation from the protocol must be fully explained and documented by the Investigator.

The Investigator must sign the affiliated Protocol Signature Page. The signature confirms that the Investigator has reviewed, agreed and approved the requirements contained in this protocol.

### **2.5.1 Potential Risks and Benefits**

The study drug Kineret is well tested in patients with rheumatoid arthritis and a large number of placebo-controlled studies have shown Kineret to be well-tolerated. Kineret is a registered drug for patients with rheumatoid arthritis thus the side effects of Kineret are well known. The most common side effects with Kineret are headache, injection site reactions and increase in cholesterol levels. The full list of side effects is listed in the SmPc of the drug.

The inclusion and exclusion criteria for the present trial have been designed to exclude patients for whom treatment with Kineret is contradicted. The risks that the patient randomized to Kineret is exposed to in connection with the study are therefore considered small.

Patients that participate may still be exposed to potential risks in the form of unexpected side effects. Adverse events and side effects will be collected throughout the course of the study, partly through spontaneous reporting by the research person and by the Investigator and delegated study staff that gather information at the regular visits of the patients. This will enable appropriate actions to be taken to maintain patients' safety.

Potential benefits of Kineret treatment are the anticipated clinical effect to improve signs and symptoms of infection and to eradicate the infection. If Kineret is proven to be effective, patients with recurrent cystitis may have future access to better alternative treatments and improved preventive measures could also be the result. Participation in this trial is voluntary and subjects are allowed to withdraw at any time.

Participants in the trial will be under careful supervision by a qualified Investigator during the entire trial period. If any potentially serious reactions are observed, subjects will be withdrawn at the Investigator's discretion or according to withdrawal criteria (Section 5.6.1).

The risk-benefit of Kineret treatment for patients with recurrent cystitis is judged to be favourable.

Patients randomised to the control group will be treated with conventional antibiotics used for this group of patients and will not, due to the participation in this trial, be exposed to further risks than in routine praxis.

### **3 Trial Objectives and Endpoints**

The overall objective of the trial is to evaluate efficacy and safety of Kineret. Kineret will be investigated for treatment of episodes of acute cystitis in female patients with a history of recurrent cystitis, i.e. recurrent episodes of lower urinary tract infections. Kineret will be compared to conventional antibiotic treatment with Nitrofurantoin, using a randomized protocol.

### 3.1 Objectives

#### 3.1.1 Primary Efficacy Objective

To investigate treatment efficacy of Kineret compared to Nitrofurantoin in female patients with an acute episode of recurrent cystitis.

- a) To investigate whether Kineret is effective in treatment of acute cystitis.
- b) To investigate whether Kineret treatment decreases the incidence of recurrent cystitis.

#### 3.1.2 Secondary Efficacy Objectives

- a) To define the molecular mechanisms resulting in recurrent cystitis, based on animal data.
- b) To map the molecular effects of Kineret in patients with recurrent cystitis.

#### 3.1.3 Safety Objective

To evaluate the safety and tolerability of the study treatments.

### 3.2 Endpoints

#### 3.2.1 Primary Efficacy Endpoint

Reduction in symptom score measured by the ACSS in the first 5 days (ACSS dynamics).

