### **5.2 Inclusion Criteria for All Subjects**

1. Stable patients with an acute episode of recurrent uncomplicated cystitis.
2. Signed written informed consent form
3. Capability and willingness to comply with study procedures
4. Female subjects, 18 - 65 years old
5. Negative urine pregnancy test in women of childbearing potential.
6. Sum score of the main uUTI symptoms reported on the Acute Cystitis Symptom Score (ACSS) typical domain at visit 1 is  $\geq 6$
7. Typical symptoms must be acute, developed within  $\leq 6$  days
8. Historys of recurrent cystitis ( $\geq 3$  documented episodes in the history in the past year) or ( $\geq 2$  documented episodes in the history in the past 6 months))
9. Contraception

Contraception should be maintained during treatment and 30 days after last intake. Women of childbearing potential must use contraceptive methods which are considered as highly effective birth control methods. Such methods include:

- combined (estrogen and progestogen containing) hormonal contraception associated with inhibition of ovulation:
  - oral
  - intravaginal
  - transdermal

- progestogen-only hormonal contraception associated with inhibition of ovulation:
  - oral
  - injectable
  - implantable
- intrauterine device (IUD)
- intrauterine hormone-releasing system ( IUS)
- bilateral tubal occlusion
- vasectomised partner
- sexual abstinence

Hormonal contraception methods should be combined with barrier methods.

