## 9.3 Statistical Analysis

The statistical analysis will be specified in a Statistical Analysis Plan prior to Database lock. All data analysis will be based on statistical hypothesis testing. Population variables, adverse events and efficacy variables will be formally evaluated. The primary objective of the trial is to evaluate the safety and efficacy of Anakinra treatment for episodes of acute cystitis in patients with recurrent disease. No formal sample size calculation evaluating the power of the trial has been performed. However, a consideration regarding the sample size was made based on previous studies of Anakinra in a murine acute cystitis model. For efficacy, the sample size was based on analysis of symptom scores, inflammatory parameters and bacterial cultures. A sample size of 20 patients in the Anakinra treatment group and ten in the group receiving antibiotics was deemed suitable to achieve criterion for significance (alpha) 0.05 and power 90% using the paired samples 1-tailed t-test. The null hypothesis is H0: mean change in symptom score = 0 and the alternative hypothesis is HA: mean change in symptom score > 0.

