|                                   | 5 Schmerzen oder Beschwerden (unangenehmes Druckgefühl) im Unterbauch oder Beckenbereich                                                                                                                                                                                  |  Nein                                                                                                                                                                                                                                                                                                                                                                                               |  Ja, wenig                                              |  Ja, mäßig                                       |  Ja, stark                               |
|                                   | 6 Sichtbares Blut im Urin                                                                                                                                                                                                                                                 |  Nein                                                                                                                                                                                                                                                                                                                                                                                               |  Ja, wenig                                              |  Ja, mäßig                                       |  Ja, stark                               |

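### Testing ACSS reduction against zero shows neither efficacy relative to nitrofurantoin nor symptom resolution, and comparing reductions adds avoidable noise from entry severity

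*Protocol*

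**What the plan says.** Section 3.2.1 gives the primary endpoint as "Reduction in symptom score measured by the ACSS in the first 5 days", followed in brackets by the term ACSS dynamics. No domain, target score or resolution criterion follows.

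Section 5.2 admits patients on this basis: "Sum score of the main uUTI symptoms reported on the Acute Cystitis Symptom Score (ACSS) typical domain at visit 1 is" at least 6, with no upper limit. In the questionnaire in Section 22.3 the typical domain has six items, the last being "6 Sichtbares Blut im Urin", each scored 0 to 3.

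Section 9.3 states "The null hypothesis is H0: mean change in symptom score = 0", with the alternative that it exceeds zero. The sample size, "A sample size of 20 patients in the Anakinra treatment group and ten in the group receiving antibiotics", is said to meet "criterion for significance (alpha) 0.05 and power 90% using the paired samples 1-tailed t-test".

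Section 3.1.1 sets the primary objective as efficacy compared with nitrofurantoin. Section 2.1 puts the question as "We want to investigate whether the treatment provides adequate cure for acute cystitis compared to conventional antibiotic treatment", judged on symptoms, inflammation and bacteria. The secondary endpoints in Section 3.2.3 cover bacteriuria, leucocyturia, recurrence and molecular assays; none counts patients whose symptoms resolved.

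**The concern.** There are two separate problems.

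First, the stated test does not match the question. Every patient enters with an acute episode and receives active treatment, so a mean fall from Day 1 is to be expected in either arm. Showing that it exceeds zero gives no contrast with the antibiotic, and it can succeed while many patients still have substantial symptoms.

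Second, the largest reduction a patient can record is her own entry score. A patient going from 16 to 8 records 8 points and still meets the entry score. One going from 7 to 0 records 7 points and is symptom-free. If reductions are compared between arms without regard to Day 1, chance differences in entry severity pass into the result, and ten patients in one arm leave room for such differences.

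**Working it through.** **Inputs.** Entry score at least 6 (Section 5.2); six items scored 0 to 3 (Section 22.3); 20 and 10 patients, alpha 0.05, one-tailed paired t-test, 90% power (Section 9.3). The protocol gives no mean or SD for the baseline score or the change, so all such values below are assumptions.

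**The plan's own figure.** The 90% power cannot be reproduced, because no effect size or SD is stated. Solving the noncentral t distribution for the standardised change (mean divided by SD of change) that gives 90% power:
- paired t-test, one-sided, n = 20: 0.68
- paired t-test, one-sided, n = 10: about 1.0

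With an assumed SD of change of 3 to 4 points, 0.68 is a mean fall of 0.68 × 3 = 2.0 to 0.68 × 4 = 2.7 points. From an assumed mean entry score of 12, the mean on Day 5 would be about 9.3 to 10.0, still above the entry threshold of 6. The stated test can therefore succeed without resolution.

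**Range of possible reductions.** Maximum score 6 × 3 = 18, so entry scores run from 6 to 18, and so do the caps on reduction.

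**Noise from entry severity.** Take the limiting case in which all 30 patients reach 0 on Day 5. Each reduction then equals that patient's baseline, and the true difference in Day 5 outcome is nil. The standard error of the between-arm difference in mean reduction is SD × √(1/20 + 1/10) = SD × 0.387.

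| Assumed baseline SD | SE (points) | 1.96 × SE |
|---|---|---|
| 2 | 0.77 | 1.5 |
| 3 | 1.16 | 2.3 |
| 4 | 1.55 | 3.0 |

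In the same case the Day 5 scores are identical in both arms, so an analysis of Day 5 score adjusted for Day 1 returns a difference of exactly zero.

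**What a between-arm test can detect.** An unadjusted two-sample t-test with 20 v 10 needs a standardised difference of 1.16 (one-sided) or 1.30 (two-sided) for 90% power. At 0.68 its power is 53% or 40%. The stated 90% therefore does not carry over to the comparison that the objective asks for.

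**The other reading of the endpoint.** ACSS dynamics could point to the item headed Dynamik, scored 0 to 4, whose category 0 is complete disappearance of symptoms. That item appears only in the follow-up form (Part B). It has no Day 1 value, so neither a reduction nor a mean change can be computed from it. The score-change reading is the only one that fits Sections 3.2.1 and 9.3, but the wording leaves both terms standing.

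**The case against.** The strongest reply has four parts.

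- The trial is described as a pilot looking for first signs of efficacy, the word cure comes from the background section, and bacteriuria and leucocyturia cover the bacterial and inflammatory sides. This stands in part: the trial does not neglect cure altogether. The symptom side, however, has no resolution endpoint, and the formal objective is still comparative.
- Adjustment for baseline is commonly left to the SAP, which is not shown. That is fair, and its absence alone would be no finding. The point is what the protocol does fix: a within-group null of no change, stated as the hypothesis for a comparative objective.
- Randomisation balances entry scores in expectation, and a valid confidence interval already includes the chance imbalance. This is correct. A reader might infer from the 16-to-8 and 7-to-0 example that the comparison of means is biased. It is not; the example limits how a reduction can be read as cure, and the imbalance costs precision.
- The limiting case and the SDs are assumed. An SD of 4 exceeds that of a uniform spread over 6 to 18 (√14 = 3.74), so the top of the range would need scores piled at both ends.

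A reader might also infer that the trial cannot show cure at all. The documents do not support that: the ACSS is completed by both arms on Day 1, Day 5 and at Visit 6, and urine is cultured at those visits.

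**Conclusion.** The point holds for the primary endpoint and test as worded, not for the trial's data. Rejecting a zero mean change establishes neither efficacy relative to nitrofurantoin nor symptom resolution. An unadjusted comparison of reductions would also carry avoidable imprecision from entry severity, up to an SE of about 1.16 points at a baseline SD of 3 (0.77 to 1.55 for SD 2 to 4). That size rests on assumed SDs and on the limiting case in which all symptoms clear; the mismatch between test and objective rests on no assumption. It should be corrected, since the Day 1 and Day 5 scores needed are already collected.

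**What to change.** - **Section 3.2.1:** state that the measure is the ACSS typical-domain sum score, and remove the added term or reconcile it with the Part B item.
- **Section 9.3:** make the primary analysis the between-arm difference in Day 5 score adjusted for Day 1 score, for example by ANCOVA, with a 95% CI. Restate the hypothesis accordingly and drop the 90% power claim unless it is justified for this contrast.
- **Section 3.2.3:** add a supportive, descriptive secondary endpoint by arm at Day 5 and Visit 6: the proportion with few or no remaining typical symptoms (for example sum 0 to 1, or Dynamik category 0) and no non-study antibiotic. The antibiotic condition matters because Section 6.2 keeps treatment failures in the study on other antibiotics. A sum below 6 should not serve alone, since a change from 6 to 5 would count as resolved.

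**Cost.** This is a change of wording, with no new visits or questionnaires. One check is needed: Section 6.7 limits recording of concomitant medication in the eCRF to the period up to the last dose, while the schedule lists it at every visit. Antibiotic use up to Visit 6 must be captured. The proportion will be imprecise: with assumed resolution rates of 80% v 50%, power at 20 v 10 is about 34%, and for 80% v 60% about 17% (two-sided 0.05). It supports the score analysis and does not replace it.
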